## Abstract

**Background:**

In the first year after childbirth, 94% of women experience one or more major health problems (urinary incontinence, faecal incontinence, perineal pain, back pain). Difficulties in intimate partner relationships and changes affecting sexual health are also common. The aim of this study is to investigate changes in women's health from early pregnancy until four years after the birth of a first child.

**Methods/design:**

The Maternal Health Study is a longitudinal study designed to fill in some of the gaps in current research evidence regarding women's physical and psychological health and recovery after childbirth. A prospective pregnancy cohort of >1500 nulliparous women has been recruited in early pregnancy at six metropolitan public hospitals in Melbourne, Australia between April 2003 and December 2005. In the first phase of the study participants are being followed up at 30–32 weeks gestation in pregnancy, and at three, six, nine, 12 and 18 months postpartum using a combination of self-administered questionnaires and telephone interviews. Women consenting to extended follow-up (phase 2) will be followed up six and 12 months after any subsequent births and when their first child is four years old. Study instruments incorporate assessment of the frequency and severity of urinary and bowel symptoms, sexual health issues, perineal and abdominal pain, depression and intimate partner violence. Pregnancy and birth outcome data will be obtained by review of hospital case notes.

**Discussion:**

Features of the study which distinguish it from prior research include: the capacity to identify incident cases of morbidity and clustering of health problems; a large enough sample to detect clinically important differences in maternal health outcomes associated with the method of birth; careful exposure measurement involving manual abstraction of data from medical records in order to explore mediating factors and possible causal pathways; and use of a variety of strategies to improve ascertainment of health outcomes.

## Background

In the 1990s two large hospital cohort studies in the UK and a population-based Australian cohort study drew attention to the significant burden of physical ill health among women in the year after giving birth [1-3]. Common experiences highlighted by these studies include back pain, exhaustion, urinary and anal incontinence, constipation, haemorrhoids and persisting perineal pain. There is also mounting evidence regarding changes affecting women's sexual health during and after pregnancy [3-5], and about the impact of intimate partner violence on childbearing women [6-8].

This research heightened awareness of the extent of maternal morbidity after childbirth and contributed to debate concerning the contribution of pregnancy and birth events to longer term health outcomes, such as prolonged perineal pain and dyspareunia, urethral and anal sphincter damage, genital prolapse, and urinary and anal incontinence [9-15]. There is now a growing literature comparing maternal health outcomes following spontaneous and operative vaginal births with elective and emergency caesarean section.

Despite an increasing number of studies examining obstetric risk factors for individual morbidities such as urinary and anal incontinence, evidence concerning risks associated with operative vaginal birth and caesarean section remains inconclusive. Limitations of the existing literature include: lack of study power for assessing key obstetric exposures (e.g. method of birth) or mediating factors (e.g. perineal trauma); study designs that do not facilitate reliable identification of incident cases, i.e. the onset of symptoms during pregnancy or the first few months after giving birth; inadequate follow-up periods (few studies extend beyond 6–12 months postpartum); and a tendency to focus on individual morbidities, such as urinary incontinence or anal incontinence, ruling out assessment of combined morbidities or a more comprehensive assessment of women's general health following childbirth.

The Maternal Health Study is a longitudinal cohort study investigating the health and well-being of nulliparous women during pregnancy and after the birth of their first child. Recruitment to the study commenced in 2003 and was completed in December 2005. The study is designed to address gaps in current research evidence regarding women's physical and psychological health and recovery after childbirth. In the first phase of the study women are being followed from early pregnancy (≤20 weeks gestation) through to 18 months postpartum. Women consenting to participate in extended follow-up (phase 2) will be followed up six and twelve months after any subsequent births, and when their first child is four years old. This paper outlines the study methods and design considerations for phase 1 of the study.

## Methods/design

### Aims

Specific aims in phase 1 of the study are:

1. To measure the incidence and natural history (onset, severity, and duration) of maternal health problems, in particular urinary incontinence, anal incontinence, perineal pain, sexual health issues, and depression among women having their first child.

2. To explore the contribution of obstetric risk factors; in particular obstructed labour, method of birth, and degree of perineal trauma, to postpartum health problems, taking into account early pregnancy health status.

3. To investigate reasons for non-disclosure of maternal health problems, and for the limited use of primary and specialist health services for specific postpartum health issues.

### Study hypotheses

Pre-specified study hypotheses are:

1. That vaginal birth assisted by forceps or vacuum extraction is an independent risk factor for incident cases of urinary incontinence, anal incontinence, persisting perineal pain and sexual problems after birth.

2. That both mediolateral episiotomy and midline episiotomy are independent risk factors for incident cases of urinary incontinence, anal incontinence, persisting perineal pain and sexual problems after spontaneous vaginal birth.

3. That mediating factors for urinary incontinence, anal incontinence, persisting perineal pain and sexual problems after spontaneous and assisted vaginal births include fetal size (≥ 4000 grams), maternal size (≤ 150 cm, BMI ≥ 30), length of labour, partogram evidence of obstructed labour, lithotomy position or upright position of the mother during late labour and birth, and non-suturing of perineal tears.

4. That these mediating factors will differ in their strength of association with urinary incontinence, anal incontinence, persisting perineal pain and sexual problems leading to new hypotheses about causal pathways.

5. That the number and severity of physical health problems in the year after birth will increase the probability of women becoming depressed or remaining depressed.

6. That socio-economic factors such as low income, single marital status and non-English speaking background will increase the probability of women becoming depressed or remaining depressed, taking obstetric history into account.

7. That women who have not disclosed health problems to their GP or specialist obstetrician will be willing to discuss the reasons for non-disclosure in a telephone interview.

8. That the reasons for non-disclosure will include: the perception that the problem is 'natural', to be expected after childbirth, too embarrassing to discuss, not a medical problem, or that nothing can be done about it; fear of medical tests and investigations; fear of surgery; fear that treatment might make it worse; fear that treatment might create new problems; fear that the problem will not be regarded as a significant health issue by health professionals.

9. That socio-economic factors such as low income, single marital status, and non-English speaking background will decrease the probability of women experiencing physical and emotional health problems disclosing these health problems to primary and specialist health professionals.

### Sample

Recruitment of nulliparous women booking to give birth at five metropolitan public hospitals in Melbourne, Australia commenced in April 2003. Participating hospitals have a mix of high and low risk perinatal services. Two hospitals are tertiary level centres with neonatal intensive care (NICU) facilities.

Eligibility criteria for the cohort are: age ≥18 years; nulliparity; estimated gestation 10–20 weeks of pregnancy (according to date of last menstrual period or ultrasound) at enrolment; sufficient proficiency in English to complete telephone interviews and written questionnaires. Criteria for exclusion after study enrolment are: spontaneous abortion prior to 20 weeks gestation; ectopic pregnancy; termination of pregnancy prior to 20 weeks gestation. Women who experience a multiple pregnancy, a stillbirth or neonatal death or a serious maternal illness (e.g. psychotic illness, severe pre-eclampsia) will not be excluded from participation in the cohort, but may be excluded from some analyses.

### Sample size

Sample size calculations were conducted using Epi Info Version 5 based on prevalence estimates for primary outcomes derived from a population-based Victorian survey of recent mothers [16]. Table 1 shows power calculations for the study with alpha of 0.5 and beta of 0.20, assuming ratios of:

**Table 1 T1:** Sample size calculations

**Exposure comparison (ratio of unexposed: exposed)**	**Outcome of interest**	**Difference**	**Sample size estimate**	**Total number required***
**Spontaneous vaginal birth:forceps/vacuum extraction (2:1)**	Urinary incontinence Faecal incontinence Sexual problems Perineal pain	11% versus 18% 2.6% versus 8% 24% versus39% 20% versus 53%	930 642 360 168	1200 800 450 210
**Emergency caesarean:forceps/vacuum extraction (1:2)**	Urinary incontinence Faecal incontinence Sexual problems	7% versus 18% 3.9% versus 10.5% 29% versus 39%	371 573 841	950 1500 2200
**Elective caesarean:forceps/vacuum extraction (1:5)**	Urinary incontinence Faecal incontinence Sexual problems	2.4% versus 18% 2.8% versus 10.5% 27% versus 39%	276 763 938	900 2500 3100

* Taking into account the relative frequency of different methods of delivery

• 2:1 (unexposed:exposed) for comparison of spontaneous vaginal births with operative vaginal births;

• 1:2 for comparison of emergency caesarean sections with operative vaginal births; and

• 1:5 for comparison of elective caesarean sections with operative vaginal births.

These ratios were based on routinely collected data for women giving birth in Victoria in 1999. Since the five study hospitals are all public hospitals and nulliparity was an eligibility criterion for the study, the ratios were calculated based on confinements of women admitted as public patients for the birth of their first child.

Using these parameters and allowing for 20% loss to follow-up by 18 months postpartum, we estimated that a sample of 1,900 women would be sufficient to test the hypothesis that primiparous women having an operative vaginal birth have a twofold greater relative risk of developing urinary incontinence, faecal incontinence and sexual problems compared with women having a spontaneous vaginal birth, and to detect a relative risk of 2.0 for urinary incontinence for all exposure comparisons.

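### Table 1 gives the forceps/vacuum group two different faecal incontinence risks (8% and 10.5%), and the emergency caesarean figure of 573 does not follow from the method that reproduces most of the table

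*Protocol article*

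**What the plan says.** In the Sample size section of the protocol article, Table 1 compares forceps/vacuum births with three other groups: spontaneous vaginal births, emergency caesareans and elective caesareans.

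- Against spontaneous birth, the first two rows (urinary, then faecal incontinence) read "11% versus 18% 2.6% versus 8" per cent.
- Against emergency caesarean, the three rows (urinary, faecal, sexual) read "7% versus 18% 3.9% versus 10.5% 29% versus 39" per cent.
- Against elective caesarean, the faecal incontinence row reads "2.8% versus 10.5" per cent.

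The ratio for the middle block is given as "1:2 for comparison of emergency caesarean sections with operative vaginal births". Its faecal incontinence row shows 573 in the pair and 1,500 in total. The total column is footnoted "Taking into account the relative frequency of different methods of delivery". The error rates are printed as "alpha of 0.5 and beta of 0.20". The software is named ("Sample size calculations were conducted using Epi Info Version 5"), but neither sidedness nor any continuity correction is stated.

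The closing sentence of the section, allowing for 20% loss, says 1,900 women suffice for urinary incontinence, faecal incontinence and sexual problems against spontaneous birth, and for urinary incontinence in every comparison.

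**The concern.** Forceps/vacuum is one group, so its faecal incontinence risk should be the same whichever group it is compared with. Two risks are used without comment, although all prevalence estimates are attributed to one survey. The caesarean rows therefore rest on a larger assumed difference than 8% would give.

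The emergency caesarean row also looks as though it was not calculated like its neighbours. This matters because of where 1,500 falls: 1,900 less 20% leaves 1,520 women, so as printed that comparison seems just within reach. Faecal incontinence is a main outcome, the Data analysis plan reports outcomes separately for both kinds of caesarean, and Strengths and limitations describes the sample as large enough for comparisons by method of birth. Readers will use Table 1 to judge that.

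**Working it through.** **Inputs.** Risks, ratios and printed sizes are from Table 1. Power is 80%. Alpha is taken as 0.05 two-sided; this is an assumption, since 0.5 is printed but 0.05 reproduces the table. The continuity correction is also an assumption, judged by fit.

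**Formula (Fleiss).** Let p1 be the risk in the comparison group, p2 the risk in forceps/vacuum, k the number of forceps/vacuum births per comparison birth, d = |p1 − p2| and p̄ = (p1 + k·p2)/(1 + k).

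- Uncorrected: m = [1.960·√((1 + 1/k)·p̄(1 − p̄)) + 0.842·√(p1(1 − p1) + p2(1 − p2)/k)]² / d²
- Corrected: n1 = (m/4)·[1 + √(1 + 2(1 + 1/k)/(m·d))]², with n2 = k·n1

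**Step 1: reproduce the table at the stated ratios, each group rounded up.**

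| Comparison group, outcome | Printed | Corrected | Uncorrected |
|---|---|---|---|
| Spontaneous, urinary | 930 | 930 | 867 |
| Spontaneous, faecal (8%) | 642 | 644 | 564 |
| Spontaneous, sexual | 360 | 360 | 330 |
| Spontaneous, perineal pain | 168 | 84 | 71 |
| Emergency, urinary | 371 | 372 | 333 |
| **Emergency, faecal (10.5%)** | **573** | **633** | **567** |
| Emergency, sexual | 841 | 843 | 798 |
| Elective, urinary | 276 | 276 | 234 |
| Elective, faecal (10.5%) | 763 | 744 | 654 |
| Elective, sexual | 938 | 942 | 882 |

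The corrected formula matches eight of the nine other rows within 3%. Perineal pain is the exception. The uncorrected formula falls clearly below print in all nine.

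**Step 2: the 573.**

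- Stated ratio (k = 2), corrected: p̄ = 0.083, d = 0.066, m = 188.8, n1 = 210.9. That is 211 + 422 = 633. Letting both risks vary within their rounding gives 618 to 654, which does not reach 573.
- Inverted ratio (k = 0.5), corrected: p̄ = 0.061, m = 337.3, n1 = 381.4. That is 382 + 191 = 573, exactly as printed.
- Stated ratio, uncorrected: 189 + 378 = 567. The rounding range is 552 to 585, which includes 573.

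At 191 emergency caesareans and 382 operative births, power is 80.5% without the correction and about 75% with it.

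**Step 3: the total.** With 5 operative births, the three ratios imply 10 spontaneous births, 2.5 emergency caesareans and 1 elective caesarean, or 18.5 in all.

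- By ratio: 633 ÷ (7.5/18.5) = 1,561.
- By the row's own printed fraction: 633 × 1,500/573 = 1,657.

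Both exceed 1,520. Without the correction, 567 × 1,500/573 = 1,484, which does not.

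**Step 4: one risk throughout (corrected formula).**

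- The 8% was really used as an input: it gives 644 against 642 printed, whereas 10.5% would give 371.
- 8%, emergency (3.9% versus 8%, 1:2): 443 + 886 = 1,329. Total 1,329 ÷ (7.5/18.5) = 3,278, or 1,329 × 1,500/573 = 3,479. Printed: 1,500.
- 8%, elective (2.8% versus 8%, 1:5): 217 + 1,085 = 1,302. Total 1,302 ÷ (6/18.5) = 4,014, or 1,302 × 2,500/763 = 4,266. Printed: 2,500.
- 10.5% throughout: only the spontaneous row changes, from 642 to 371.

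**The case against.** The strongest reply is that nothing the authors claim for 1,900 women depends on these rows. The closing sentence claims faecal incontinence only against spontaneous birth, where the table uses the less favourable 8%. The largest total among the comparisons it names is 1,200, and 1,200/0.8 = 1,500 recruits, below 1,900. Table 1 itself shows other rows out of reach (2,200, 2,500 and 3,100), so the authors did not present every row as powered. All of this stands.

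It can also be said that the table is too irregular to identify a mechanism from one exact match, since perineal pain is off by a factor of two and elective faecal incontinence by about 3%. That stands in part. A reader might infer that 573 can arise only from an inverted ratio, but the uncorrected formula at the stated ratio comes within about 1%, and the article does not say which formula was used. Dropping the correction would, however, mean a change of method for this one row, and 567 is still not the printed number.

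Finally, the two risks might reflect different definitions in the source survey. That cannot be checked from the article, which gives no such reason.

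**Conclusion.** Two defects stand. First, the 8% and 10.5% are unreconciled, and the choice matters: it roughly doubles the emergency caesarean requirement or cuts the spontaneous birth requirement by more than 40% (642 to 371). Second, 573 is inconsistent with the method that fits eight of the other nine rows, which gives 633 and a total of about 1,560 to 1,660. The second point assumes two-sided alpha of 0.05 and the continuity correction. Inversion of the ratio is the likely cause, not a proven one.

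Three stronger readings are not supported:

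- That 1,500 is too low whatever the method. It is too low under the correction used elsewhere in the table, but adequate without it.
- That the 1,500 set the recruitment target. 1,500/0.8 = 1,875 is close to 1,900, but the article does not make that link and justifies 1,900 by other comparisons.
- That the 1,900 claim for faecal incontinence against spontaneous birth fails. It holds with either risk.

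What changes is how Table 1 should be read for faecal incontinence against caesarean birth. With the table's usual method, neither caesarean comparison is within reach of 1,520 analysed women, and the shortfall is large if 8% is the right risk.

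**What to change.** 1. Use one faecal incontinence risk for forceps/vacuum in all three blocks, or state why the risks differ.
2. Recompute the faecal incontinence rows at the stated ratios with one named method, giving sidedness and whether a continuity correction is applied.
3. Correct the total column to match. With 10.5% kept, the emergency caesarean row becomes 633 and about 1,560 to 1,660.
4. Add a sentence that faecal incontinence against either caesarean group is not among the comparisons 1,900 women are shown to support.

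The cost is a corrected table and one sentence. Recruitment has closed, and no extra women or change of conduct is needed. The stated caesarean figures for faecal incontinence become less favourable, markedly so if 8% is right.

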### Data analysis plan

For aim 1 (incidence, severity and duration of maternal health problems):

▪descriptive frequencies and 95% confidence intervals will be calculated for outcomes of interest at baseline and each follow-up, with stratification to determine the extent of clustering of morbidities and to control for timing of onset of symptoms (prior to pregnancy, during pregnancy, after the birth).

For aim 2 (contribution of pregnancy and birth events to subsequent morbidity):

▪proportions of women reporting outcomes of interest by method of birth (spontaneous vaginal births, forceps assisted vaginal births, vacuum extraction, elective caesarean section, emergency caesarean section) and other obstetric risk factors, including: prolonged first stage labour, fetal position during labour, evidence of obstructed labour in second stage; duration of pushing; fetal presentation at delivery, maternal birth position; use of epidural, spinal or general anaesthesia; degree of perineal trauma; infant birthweight; head circumference; gestation at delivery.

▪multivariable analysis will be undertaken to assess the extent to which method of birth makes an independent contribution to each outcome variable, and to combined morbidity (eg. combined faecal and urinary incontinence). Covariates will include significant labour and birth events, timing of onset of symptoms (pre-pregnancy/during pregnancy/post birth), maternal age and maternal height and early pregnancy BMI. A series of stratified and logistic regression analyses will be performed to validate model choices against stratified data. Generalised linear mixed modelling to take account of repeated measures will be used to determine the effect over time on the associations between health outcomes and covariates.

For aim 3 (reasons for non-disclosure of morbidity to health professionals): descriptive frequencies for prevalent cases will be reported for formal and informal help-seeking and treatment, and for non-disclosure at baseline and each follow-up. Analysis will take into account socio-economic background, the severity and duration of maternal health problems, general health status (SF-36) and extent of co-morbidity.

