### Analysis considerations

A major challenge in planning analyses assessing causal pathways is the extent to which obstetric risk factors are linked, and the associated difficulty in analysis of sorting out the impact of method of birth (as the 'exposure of main interest') from other exposure and treatment effects. Recently there has been much debate about the possible benefits of elective caesarean section in protecting women's pelvic floor and preventing urinary incontinence [9-12]. Although sample size calculations for the study were not based on comparisons of spontaneous vaginal birth with elective caesarean section, the study will have adequate power for this comparison. Additional file 1 (table 2) and 2 (table 3) provide a summary of pregnancy and birth cohort studies which have assessed the role of obstetric factors for urinary incontinence in pregnancy and after childbirth. Most of the included studies with data on operative births report that caesarean section is protective against urinary incontinence after childbirth compared with vaginal birth [see Additional File 1 and Additional File 2]. However, few of these studies incorporate comprehensive assessment of obstetric risk factors. Only half of the included studies obtained information on obstetric events by reviewing medical case notes [34-36,38,42,45,47,49,50,52-54], and two of these studies relied in part on information obtained from computerised records [53,54]. Many studies do not differentiate women who have an emergency caesarean section in labour from those having an elective caesarean section prior to commencement of labour [36,38-40,46,48,51-54]. Less than half include measures of fetal or infant size [34-36,45,47,48,53,54], maternal size (height, pre-pregnancy BMI) [34,36,48,50,52-54], or genital tract trauma [34,45,47-49,52-54], and only a handful of studies include data on use of analgesia and anaesthesia [43,50,52-54], fetal position in labour [35,39,50] or maternal position in second stage [53]. In contrast, duration of second stage labour is commonly collected as a proxy variable for obstructed labour [33-36,39-41,43,48-51,53,54]. Inconsistencies in the way information on length of labour is recorded, and lack of data on other indicators of possible obstructed labour (e.g. position of the fetus, descent of the fetal head) make it difficult to interpret this data.

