Figure 2 provides a schematic overview of key covariates that will be considered in analysis. The arrows represent possible causal associations between covariates based on available epidemiological evidence regarding obstetric risk factors for maternal morbidity. Planning analyses using causal acyclic diagrams has been advocated by Greenland and others as a useful strategy for identifying variables that may mediate or moderate the relationship between an exposure of main interest and primary health outcome/s [55,56]. Figure 2 illustrates the complexity of possible causal pathways and relationships between obstetric risk factors for maternal morbidity. Considering our hypothesis that vaginal birth assisted by forceps or vacuum extraction is an 'independent' risk factor for urinary incontinence, the diagram illustrates the multiple covariates and combinations of covariates preceding the delivery and subsequent to delivery that may mediate the relationship between the mode of birth and the outcome of urinary incontinence. To take one example, the estimated size of the fetus as large for gestational age might lead directly to the decision to conduct an elective caesarean section, or alternatively, via a range of possible pathways to obstruction in second stage labour and a vaginal birth assisted by forceps or vacuum extraction or an emergency caesarean section. A number of other factors may influence the outcome, including the position of the fetus in second stage labour, length of time in active second stage, whether or not an episiotomy is cut and the extent of other genital tract trauma. The conventional statistical approach – used by many researchers – of adjusting for those covariates such as infant size for which data are available is likely to lead to erroneous conclusions. This is not only because data are rarely available for the full range of covariates illustrated in Figure 2, but also because such analyses fail to consider the complex range of possible pathways involved. Simple adjustment for fetal size assumes that the impact will be the same irrespective of other aspects of labour and birth. Biologically this seems somewhat implausible given the extra pressure on the pelvic floor associated with a long labour and large baby often in occipito-posterior position. While these other factors can also be adjusted for in analysis, it may be more useful to conduct separate analyses restricted to women who do and do not experience labour. This is likely to yield less biased estimates of effect for specific causal pathways [57]. The timing of onset of symptoms (and symptom resolution) presents further challenges in analysis. Separate stratified analyses will be performed for incident and prevalent cases of morbidity.

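### Conclusions about elective caesarean itself need a contrast with planned vaginal birth; the comparators now named are defined by how labour ended

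*Protocol article*

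**What the plan says.** All places are in the protocol article.

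- **Sample size (Table 1 and ratio list).** There are three comparisons, each with forceps/vacuum birth as one arm. Spontaneous births are set at two for every assisted birth, and emergency caesareans at one for every two. The elective ratio is "1:5 for comparison of elective caesarean sections with operative vaginal births". The table heads these ratios as unexposed to exposed, so elective caesarean enters as an unexposed reference group.
- **Data analysis plan, aim 2.** Outcomes are tabulated "by method of birth (spontaneous vaginal births, forceps assisted vaginal births, vacuum extraction, elective caesarean section, emergency caesarean section". These are five achieved modes. The multivariable model for method of birth takes important labour and birth events among its covariates.
- **Analysis considerations.** The text notes "much debate about the possible benefits of elective caesarean section" for the pelvic floor and urinary incontinence. It says the sample size was not built on spontaneous birth versus elective caesarean, but that power for that comparison will be adequate.
- **Analysis considerations, on Figure 2.** A large fetus "might lead directly to the decision to conduct an elective caesarean section", or may lead by other routes to an assisted birth or an emergency caesarean. Separate analyses of women who do and do not labour are suggested as possibly more useful than adjustment.

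**The concern.** Elective caesarean is settled before labour, as the Discussion itself recognises. At that point the alternative is a labour whose ending is unknown: spontaneous birth, assisted birth or emergency caesarean. Restricting the comparator to labours that ended spontaneously leaves out the women whose labours went on to intervention. Restricting it to labours that ended in forceps or vacuum keeps only some of those women. Each choice conditions on something that happens after the decision.

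The proposed split by labour does not repair this. It places elective caesarean and its alternative in different strata and does not compare them. Adjusting for labour events does not help either, because such events follow the decision and largely do not exist for women delivered before labour.

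What is at stake is the size of any benefit attributed to elective caesarean, and whether one is inferred at all for faecal incontinence and sexual problems.

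**Working it through.** **Inputs.** Rates are from Table 1. Group weights come from the three ratios, with assisted birth set to 1: spontaneous 2, assisted 1, emergency caesarean 0.5, elective caesarean 0.2, total 3.7. Elective caesarean is then 0.2/3.7 = 5.4% of births. Table 1's own inflation gives a similar share: 276/900 = 30.7% for elective plus assisted, and one sixth of that is 5.1%.

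**Step 1: reproduce the elective rows.** The article prints "alpha of 0.5 and beta of 0.20", but the table reproduces only with a two-sided alpha of 0.05. With r = 5 and pooled rate p = (p1 + r·p2)/(1 + r):

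n = [1.96·√((r+1)·p(1−p)) + 0.84·√(r·p1(1−p1) + p2(1−p2))]² / [r(p1−p2)²]

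The continuity-corrected size is n′ = (n/4)·[1 + √(1 + 2(r+1)/(n·r·|p1−p2|))]², and the total is 6n′.

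For urinary incontinence (2.4% v 18%), n′ = 46 and the total is 276, as printed. Faecal incontinence gives 744 (printed 763) and sexual problems 942 (printed 938). All are within 3%.

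**Step 2: implied planned-vaginal risk** = (2 × spontaneous + 1 × assisted + 0.5 × emergency)/3.5.

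- Urinary: (2×11 + 18 + 0.5×7)/3.5 = 43.5/3.5 = 12.4%
- Faecal: (2×2.6 + 8 + 0.5×3.9)/3.5 = 15.15/3.5 = 4.3%. With 10.5% for assisted birth, 17.65/3.5 = 5.0%. Table 1 uses both 8% and 10.5%.
- Sexual problems: (2×24 + 39 + 0.5×29)/3.5 = 101.5/3.5 = 29.0%

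**Step 3: comparator minus elective caesarean, in percentage points.**

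| Outcome (elective rate) | v assisted | v spontaneous | v planned vaginal |
|---|---|---|---|
| Urinary incontinence (2.4%) | 15.6 | 8.6 | 10.0 |
| Faecal incontinence (2.8%) | 5.2 to 7.7 | −0.2 | 1.5 to 2.2 |
| Sexual problems (27%) | 12 | −3 | 2 |

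**Step 4: power.** Two analysed totals are used: 1,900 × 0.8 = 1,520 as planned, and 1,500 × 0.8 = 1,200 if the cohort of just over 1,500 loses the assumed 20%. Elective, spontaneous and planned-vaginal groups are then about 65, 649 and 1,135 at 1,200, and 82, 822 and 1,438 at 1,520. For urinary incontinence, Fisher's exact test at two-sided 0.05, unadjusted, gives:

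| Comparator | 1,200 analysed | 1,520 analysed |
|---|---|---|
| Spontaneous birth | 63% | 80% |
| Planned vaginal birth | 80% | 91% |

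Against planned vaginal birth, a normal approximation gives 5% to 7% (1,200) and 6% to 9% (1,520) for faecal incontinence, and about 5% at both sizes for sexual problems. Fisher's test also stays below 10%. By the Step 1 formula with r = 17.5, 80% power needs 1,369 analysed women for urinary incontinence, 13,302 to 25,326 for faecal incontinence and 78,902 for sexual problems.

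**Step 5: sensitivity.** Leaving emergency caesareans out altogether gives 13.3%, 4.4% to 5.2% and 29.0%. The conclusions do not change.

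**The case against.** The strongest reply is that Table 1 is right for its own purpose. Hypothesis 1 asks whether forceps or vacuum birth is a risk factor, elective caesarean is one reference group, and comparison by achieved mode suits that question. None of the nine hypotheses concerns choosing elective caesarean. This stands, and those contrasts should stay as they are.

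The Discussion is also careful. It separates elective from emergency caesarean, uses a causal diagram and warns against routine adjustment. For urinary incontinence, the outcome it names, its spontaneous comparator gives 8.6 points against 10.0: fairly close, and on the cautious side. That stands too.

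Two stronger readings are tempting, and the document does not support either. A reader might infer that elective caesarean is compared only with assisted birth. In fact the aim 2 plan covers all five modes, and the Discussion adds spontaneous birth. A reader might also infer that findings on elective caesarean would reverse with the comparator. Urinary incontinence keeps its direction throughout. The sign changes for the other two outcomes are 0.2 and 3 points in unadjusted planning rates; the 3-point difference would have about 9% power at 1,520, and the 0.2-point one less. The article claims no such power either: Table 1 needs 2,500 and 3,100 women for those elective rows, against a planned 1,900.

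The final choice of contrast could be left to a fuller analysis plan. But the article itself names a comparator for this debate and calls its power adequate, so the choice is open to comment.

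**Conclusion.** The point holds as a modest, inexpensive improvement, not as a defect in the hypothesis 1 comparisons. Where the Discussion turns to whether elective caesarean protects, the comparator it names is selected on how labour ended, and no planned contrast pools labours however they ended.

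For urinary incontinence the effect is on size: 8.6 points against spontaneous birth and 15.6 against assisted birth, with 10.0 as the better-targeted figure. For faecal incontinence and sexual problems, reading Table 1's elective rows as the effect of elective caesarean would suggest 5.2 to 7.7 and 12 points, where the planned-vaginal differences are 1.5 to 2.2 and 2. The study could not resolve differences that small.

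This rests on Table 1's unadjusted survey rates, on the four birth groups making up all births, on every emergency caesarean counting as a planned vaginal birth, and on 20% loss.

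**What to change.** Keep the achieved-mode contrasts and Table 1 as they are for hypothesis 1. For any conclusion about elective caesarean itself, add one contrast to the analysis plan: elective caesarean versus planned vaginal birth, the latter combining spontaneous births, assisted births and emergency caesareans in labour. Adjust it only for factors known before labour, such as maternal age, height, early pregnancy BMI and symptoms before or during pregnancy. Claim adequate power for urinary incontinence only, and report faecal incontinence and sexual problems with intervals and no such claim.

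**Cost.** Mostly a regrouping of categories already collected, plus a few sentences. The listed record items give method of birth but not planned mode. Emergency caesareans before labour must therefore be assigned from the medical record, or handled in a sensitivity analysis that counts them each way. The estimate averages over how labour ended, and confounding by the reasons for choosing elective caesarean remains. Adjustment may lower the power figures above.
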